### Analyses

We hypothesize that the active intervention arms will be superior to control, similarly effective to each other, and with some additive effect when both are delivered. Analyses will be concentrated on this hypothesis.

The study employs a cluster randomized design. The analysis will be carried out using multi-level, hierarchical, logistic regression models, with the trial arm being a physician-level variable, and the prescribing (or screening) outcome a patient-level variable. These models account for clustering of patients within practices, and the consequent lack of independence of prescribing outcomes within a given physician's place of practice [55]. No place-of-practice characteristics, aside from the arm of the trial and baseline adherence to guidelines, will be entered into the model in the primary analysis. With so many physicians randomized to each arm, we anticipate that measured and unmeasured physician factors that might affect the outcome will be equally distributed between the arms. Moreover, including more place-of-practice characteristics in the model would reduce the statistical power to detect the primary outcome.

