### Proposed sample size

We wished to have adequate power to detect modest changes in the way physicians practice. Based on the median absolute effectiveness of PEMs estimated from the Grimshaw review (8%) [7], it would be important to detect 5% and 10% absolute improvements in our target behaviours. Even 5% improvements in the prevalence of evidence-based care for these common conditions will be an important achievement, with significant health benefits for many Ontarians.

In pilot data, the baseline-prescribing rate of ACE inhibitors in persons with diabetes was 36%, and the intra-class correlation for ACE inhibitor use by patients clustered within physicians was 9.2%. With an assumption that one-half of doctors work in solo practices, we ran these data testing power at a mean of three patients and ten patients per practice. Monte Carlo simulations demonstrated that a trial with 1250 practices per arm, with 10 patients per practice and an alpha of 0.05 will provide more than 98% power to detect a 10% absolute increase in the rate of ACE inhibitor use, more than 97% power to detect a 5% absolute increase, and more than 98% power to distinguish between the effects of the combined intervention and either alone, assuming the combined effect to be additive.

Because the baseline rates of the other interventions are comparable or lower (screening for retinopathy, diuretic use, aggressive blood pressure-reducing, and cholesterol-lowering therapies), and the number of patients per practitioner with these conditions is the same or higher, we will have adequate power to detect similar absolute increases for those endpoints.

Later, with the addition (see Table 1) of two groups in the second (patient reminder note) and third (theory-based outsert) replicates, a less comprehensive, but approximate simulation suggested that the impact on power would be minor and would most certainly be greater than the often used target of 80%. The research opportunity that this modification presented was judged to outweigh the likely loss of power. Therefore, we maintained 1,250 practices in the two groups that did not receive an outsert with ***informed***, and assigned 625 practices to each of the four groups who were sent an outsert.

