### Recruitment, compliance, loss to follow-up, and drop-out

Practitioners may of course decide to ignore the PEMs or never open the envelope containing ***informed***. We will not know what practitioners will do with the intervention, a normal feature of the pragmatic trial philosophy that tests interventions under real-world conditions. ***informed ***will be mailed in the usual fashion to all identified practitioners. Any practitioners who subsequently remove themselves from the mailing list for ***informed ***will be analysed in the allocated arm on an intention-to-treat basis.

While the unit of analysis is the physician, loss of patients is important to detect in order to maintain accurate denominators for the determination of outcome rates. Patients may be lost due to removal from the system (death or out-migration), or change of provider. The former will be detected in the RPDB, the latter by a plurality rule for prescriptions. For the baseline analysis (pre-intervention period), the initially assigned patients for each physician will be used. For each of the succeeding observation periods (three pre- and four post-intervention), initial patients will be confirmed by eliminating patients no longer eligible according to the RPDB, and ensuring that assigned patients are still being cared for by the study physician through a requirement that the study physician must have written the plurality of the patient's prescriptions in that period.

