## Discussion

We understand very little about the reasons for the gaps between what family practitioners do in clinical practice, and what the evidence-based ideal says they should do. The simplest intervention to narrow these gaps is the PEM, ranging from a one-sentence directive to a long guideline; and they have often been used, but in an intuitive fashion, with neither an underlying theory of behaviour change nor a deep understanding of physicians' barriers to change.

After a 1997 systematic review found their effects to be uncertain, PEMs fell into disfavour. However, a more recent and larger overview found a median improvement of 8% in comparison with no PEM – a result which was similar in effect to more expensive and intensive strategies. Nevertheless, this review cannot overcome the limitations of the primary evidence: the small number of trials (each one of which is small in size), and their continued methodological weaknesses (insufficient power to detect modest effects, and unit of analysis errors). More evidence is needed in order to decide whether PEMs can be used to help change clinical practice.

We have proposed a trial that is designed to address these shortcomings. The large size of the trial provides enough power to confidently and precisely delineate modest effects. Modest effects are important, given the large absolute impact that is achievable when the intervention is applied to a common health problem. By randomizing at the level of the physician place-of-practice, the trial avoids contamination and unit of analysis error. In addition to answering the question of whether PEMs change primary care practitioners' therapeutic decisions, this study, along with its two ancillary studies, also will compare the impact of two types of PEMs (the short, directive versus a two-page descriptive message), and will examine the contextual and sociological factors (e.g., health problems, location, style of physician practice and duration of practice) which may influence the impact of PEMs.

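### Replicate 1: adding each patient's own pre-mailing drug status to the primary model would give a small, nearly free gain in precision

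*Protocol article*

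**What the plan says.** The Analyses section specifies a multilevel logistic model with a patient-level outcome and arm as a higher-level variable. It restricts place-of-practice characteristics: none, "aside from the arm of the trial and baseline adherence to guidelines, will be entered into the model in the primary analysis". The reason given, loss of power, refers to further practice characteristics. The section is silent on patient-level covariates.

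Table 2 defines replicate 1 as prevalent diabetes at age 65 or over, with three drug-use outcomes: ACE inhibitor, two or more antihypertensives, and a lipid-lowering drug. The Outcome measurement section gives four quarters of routine data before the mailing.

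The section on recruitment, compliance, loss to follow-up and drop-out says: "For the baseline analysis (pre-intervention period), the initially assigned patients for each physician will be used". For the other periods, "initial patients will be confirmed by eliminating patients no longer eligible according to the RPDB", and the study physician must also have written the plurality of the patient's prescriptions in that period.

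The Discussion claims: "The large size of the trial provides enough power to confidently and precisely delineate modest effects".

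**The concern.** For a current-use outcome in prevalent patients, a patient's own earlier use is likely to be the strongest predictor available. The named model uses it only through a practice summary.

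If the same patients formed the baseline and the outcome, little would be lost, because arm varies between practices and the practice mean would already carry the information. The follow-up section suggests that they are not the same patients: deaths, out-migrants and those who change provider leave. The baseline mean then includes people absent from the outcome. Chance differences between practices in the prior drug use of those who stay remain in the residual.

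The width of the interval for each arm contrast in replicate 1 is at stake, including single versus combined message and insert versus outsert. Replicates 2 and 3 are not affected, since their patients are newly diagnosed or newly treated and have no earlier value of the outcome.

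**Working it through.** **1. The plan's own figure.** The inputs are in Proposed sample size: "the baseline-prescribing rate of ACE inhibitors in persons with diabetes was 36" per cent, "the intra-class correlation for ACE inhibitor use by patients clustered within physicians was 9.2" per cent, and "a trial with 1250 practices per arm, with 10 patients per practice".

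- Design effect: 1 + 9 × 0.092 = 1.828.
- Effective n per arm: 1,250 × 10 / 1.828 = 6,838.
- Standard error for 36% v 41%: √[(0.36 × 0.64 + 0.41 × 0.59) / 6,838] = 0.00831.
- Two-sided power at alpha 0.05: Φ(0.05/0.00831 − 1.96) = Φ(4.06), above 99.99%.

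The stated figure of more than 97% is met as a lower bound. For 41% v 46% (combined v single), power is also above 99.99%. With three patients per practice, power for 5 points is about 98%.

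**2. Model for the gain.** Set total variance to 1, with practice part ρ = 0.092 and patient part 0.908. The protocol's correlation is for patients within physicians; using it for practices is an assumption. Initial patients per practice are m₀ = 280,000 / (4 × 1,250) = 56. Let m₁ be the number retained. Neither before-after correlation is in the document. I assume r_c = 0.9 at practice level and r_s = 0.5, 0.7 or 0.85 for patients within practice.

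Residual variance of a practice's outcome mean:

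- A, given the baseline mean of all m₀ patients: ρ + (1−ρ)/m₁ − [r_c ρ + r_s(1−ρ)/m₀]² / [ρ + (1−ρ)/m₀].
- C, given that mean plus the retained patients' own status: ρ(1 + r_s² − 2 r_s r_c) + (1−ρ)(1−r_s²)/m₁ − ρ²(r_c−r_s)² / [ρ + (1−ρ)/m₀].
- The difference reduces to A − C = r_s²(1−ρ)(1/m₁ − 1/m₀), which is zero when m₁ = m₀.

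Example with r_s = 0.7 and m₁ = 42 (75% retained):

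- A = 0.1136 − 0.0819 = 0.0317.
- A − C = 0.49 × 0.908 × (1/42 − 1/56) = 0.0026, so C = 0.0291.
- Cut in variance: 8.4%.

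**3. Results at 56 per practice.** The half-width in percentage points for two arms of 1,250 practices is 100 × 1.96 × √(2 × residual variance × 0.36 × 0.64 / 1,250), from unrounded variances.

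| r_s | Retained | A | C | Cut in variance | Half-width |
|---|---|---|---|---|---|
| 0.5 | 48 (86%) | 0.0345 | 0.0339 | 2% | 0.699 to 0.693 |
| 0.5 | 34 (61%) | 0.0423 | 0.0397 | 6% | 0.774 to 0.750 |
| 0.7 | 48 (86%) | 0.0290 | 0.0277 | 5% | 0.641 to 0.626 |
| 0.7 | 42 (75%) | 0.0317 | 0.0291 | 8% | 0.670 to 0.641 |
| 0.7 | 34 (61%) | 0.0368 | 0.0317 | 14% | 0.722 to 0.670 |
| 0.85 | 48 (86%) | 0.0247 | 0.0228 | 8% | 0.592 to 0.568 |
| 0.85 | 34 (61%) | 0.0325 | 0.0249 | 23% | 0.678 to 0.594 |

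**4. Planning size of 10 per practice.** With r_s = 0.7, the cuts are 10%, 15% and 24% at 85%, 75% and 60% retained. The half-width falls by 0.05, 0.09 and 0.17 points.

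**5. Checks beyond the linear model.** A small logistic simulation (25 runs per scenario, so rough) gave relative efficiencies of 1.01 to 1.03 without losses and 1.07 with 20% lost. With unequal practice sizes some gain remains even without losses.

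**6. Add, do not substitute.** Over r_s 0.5 to 0.85, r_c 0.7 to 1.0 and losses of 0 to 30%, own status alone gave 0.58 to 2.25 times the variance of the planned adjustment. The practice mean should therefore stay.

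**The case against.** The strongest reply is that the quoted restriction concerns practice characteristics only. A patient's own prior use is not one, and a condensed article may leave patient-level covariates to an analysis plan. That stands. A reader might infer that the protocol excludes own status, but the text supports only that it is not named.

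A reader might also infer that the adherence covariate is defined over all initially assigned patients. The follow-up section says this of its baseline analysis, not of the model covariate. If the covariate were computed on the patients analysed, the gain would be close to nil. The Abstract also speaks of modelling four quarters before and after the mailing, so a single follow-up outcome with one summary is not established as the whole model.

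Nor is a baseline value assured for everyone. The allocation section counts any attending patient who meets entry criteria and keeps plurality-of-visits assignment for a sensitivity analysis. ODB data begin at age 65. Some patients analysed may have no earlier record.

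Finally, the effect is small against a 5-point target. In the scenarios above, some 60% to 85% of the baseline mean comes from the very patients analysed, so it already corrects for much of their prior use. All of this limits the point to a suggestion. It does not show that the planned model is the better choice.

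**Conclusion.** This is a minor, optional gain in precision, not an error. At 56 patients per practice the variance of the arm effect falls by roughly 2% to 14% for own-status correlations of 0.5 to 0.7 and retention of 60% to 85%. The gain is larger with smaller practices or more persistent drug use, and near zero if everyone is retained in equal-sized practices. The half-width shrinks by less than 0.1 point at that practice size, even in the most favourable row of the table.

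These figures rest on assumed retention and correlations, and on reading the baseline as covering all initial patients. It would be tempting to conclude that the trial's power or validity suffers. It does not: power for 5 and 10 points is unaffected, the randomised comparison is unbiased either way, and the Discussion's precision claim is not contradicted.

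**What to change.** In Analyses, for the three replicate 1 outcomes:

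- Add each patient's own status on that outcome before the mailing (yes/no), taken from a fixed window within the four pre-mailing quarters.
- Keep practice baseline adherence, and state on which patients and which period it is computed.
- Give patients without a pre-mailing value a separate missing-status category.
- Report absolute differences from the model's standardised percentages, because the odds ratio becomes conditional on prior use.

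Leave replicates 2 and 3 as they are. The cost is two or three sentences and one derived variable per outcome from claims already held, with no new data or patients. It should be fixed before outcomes are seen, since a covariate chosen later is open to challenge.

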### Subgroup analyses

Failure to consistently implement evidence into improved prescribing decisions has been associated with older physicians and those without specialty certification [56]. While we would like to test the impact of certification, no data exists describing this status that can be linked to our datasets.

Evidence-practice gaps also have been associated with physician reimbursement arrangements, patient volumes, physician gender, site and extent of training, group size, and work load [57]. Thus, we plan subgroup analyses of male versus female physicians, location of practice (urban or rural), practice volume, solo versus group practice, and years since graduation. As before, multilevel, logistic regression models will be used to assess the association between place-of-practice characteristics and target behaviours.

A further analysis of the immediate and delayed impacts of the printed educational material will be performed using time-series analysis and interventional, autoregressive, integrated moving average (ARIMA) modeling [58]. The group to which the patient's practitioner was randomized will be included as a covariate. An immediate change will be defined as a significant shift in prescribing patterns from projected estimates within four months of the intervention. Delayed effects will be measured with simple time-series analysis, such as exponential smoothing and ARIMA models by comparing actual with predicted utilization estimates. Stationarity will be assessed using the autocorrelation function and the augmented Dickey-Fuller test [59]. The auto-correlation, partial autocorrelation, and inverse autocorrelation functions will be assessed for model parameter appropriateness and seasonality. The presence of white noise will be assessed by examining the autocorrelations at various lags using the Ljung-Box test [60].

The question of whether there are differences in response to PEMs for different diseases patient health status levels and health care problems is addressed in the replicates. Differences between these replicates will be discussed, and will not *a priori *be subjected to meta-analysis. In the event of substantial homogeneity of outcomes, we will consider meta-analysis across the replicates.

There will be one analysis for each replicate upon receipt of one year of follow-up data.

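### The protocol wrongly says that adjusting for more practice characteristics would reduce power; with about 5,000 practices it costs practically nothing and may gain a little precision

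*Protocol article*

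**What the plan says.** The Analyses section plans a multilevel logistic model with arm at physician level and the prescribing or screening outcome at patient level. Apart from arm and baseline adherence, no practice characteristic enters the primary analysis. The first reason is that, with so many physicians per arm, measured and unmeasured factors should be evenly spread. The second is added to it: "including more place-of-practice characteristics in the model would reduce the statistical power to detect the primary outcome".

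The next section, Subgroup analyses, says "Evidence-practice gaps also have been associated with physician reimbursement arrangements, patient volumes, physician gender", and also with training, group size and work load. It continues: "Thus, we plan subgroup analyses of male versus female physicians, location of practice (urban or rural), practice volume", followed by solo versus group practice and years since graduation.

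Proposed sample size gives the scale. Replicate 1 rests on "a trial with 1250 practices per arm, with 10 patients per practice". For replicates 2 and 3 the authors kept 1,250 practices in each of the two groups without an outsert and "assigned 625 practices to each of the four groups who were sent an outsert".

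**The concern.** Covariates cost power mainly when clusters are few, because each term uses a degree of freedom and chance correlation with arm inflates the variance. With thousands of randomised practices that cost all but vanishes. Practice-level covariates that predict the outcome work the other way: they remove unexplained between-practice variance, which is the part of the error that more patients per practice cannot reduce. The protocol itself names such characteristics as associated with the gaps it targets.

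At stake is a modest amount of precision and the soundness of one stated reason for the primary model. The precision matters most in replicate 3, where patients per practice are few, so baseline adherence is measured poorly, and where the outsert arms were halved.

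**Working it through.** **Inputs from Proposed sample size.** "an alpha of 0.05" (taken as two-sided); "the baseline-prescribing rate of ACE inhibitors in persons with diabetes was 36" per cent; "the intra-class correlation for ACE inhibitor use by patients clustered within physicians was 9.2" per cent; 3 or 10 patients per practice; a 5-point target. Practices: 4 × 1,250 = 5,000 in replicate 1, and 2 × 1,250 + 4 × 625 = 5,000 in replicates 2 and 3. A two-arm contrast therefore has 1,250 to 2,500 practices.

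**1. The plan's own power.** Design effect = 1 + (m − 1) × 0.092, and effective n per arm = 1,250m / design effect.
- m = 10: 1.828, effective n 6,838, power for 36% v 41% is 99.997%.
- m = 3: 1.184, effective n 3,167, power 98.3%.

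The stated bound of more than 97% is met in both cases.

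**2. Cost if the added terms are useless.** With k noise covariates and N practices, the variance of the arm effect inflates by (N − 3)/(N − 3 − k). For N = 5,000 and k = 5 this is 4,997/4,992 = 1.001. Power from a noncentral t:

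| Practices | k | Variance ratio | 80% becomes | 97% becomes |
|---|---|---|---|---|
| 5,000 | 5 | 1.0010 | 79.96% | 96.99% |
| 5,000 | 20 | 1.0040 | 79.84% | 96.95% |
| 2,500 | 5 | 1.0020 | 79.92% | 96.97% |
| 2,500 | 20 | 1.0081 | 79.68% | 96.89% |
| 1,250 | 5 | 1.0040 | 79.84% | 96.95% |

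**3. Gain if they are prognostic, by formula.** The variance of a practice mean is proportional to ICC(1 − B)(1 − R²) + (1 − ICC)/m. B is the share of between-practice variance explained by baseline adherence, and R² the share of the remainder explained by the characteristics. Neither is in the protocol; assume B = 50-70% and R² = 5-20%. For m = 10, B = 0.5, R² = 0.2: (0.046 + 0.0908)/(0.0368 + 0.0908) = 0.1368/0.1276 = 1.072, so effective sample size rises 7.2%. For B = 0.7, R² = 0.05 it rises 1.2%. In standard error (SE) terms that is about 0.6% to 3.4%. With 280,000/5,000 = 56 patients per practice (replicate 1) the formula gives 3.3% to 17.4%, but power there is already near 100%.

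**4. Simulation for replicate 3.** 3,000 trials per setting, 1,250 v 1,250 practices, ICC 0.092, practice sizes varying with an assumed coefficient of variation of 0.7, weighted cluster-level regression, baseline adherence always in the model. SE in percentage points, without → with five characteristics, by assumed share of between-practice variance explained:

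| Share | One-quarter baseline | Change | Four-quarter baseline | Change |
|---|---|---|---|---|
| 0 | 0.986 → 0.988 | +0.2% | 0.939 → 0.940 | +0.1% |
| 10% | 0.988 → 0.973 | −1.5% | 0.944 → 0.935 | −1.0% |
| 20% | 0.982 → 0.950 | −3.3% | 0.925 → 0.914 | −1.2% |
| 30% | 0.986 → 0.935 | −5.2% | 0.928 → 0.899 | −3.1% |

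The steps are uneven, so single values are rough.

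**5. The planned model type.** A random-intercept logistic model was simulated with 1,250 v 1,250 practices, 10 patients each, ICC about 0.096 and 200 runs per scenario. Baseline adherence was included, and 70% of the variance not due to the characteristics was stable over time. SE of the log odds ratio: 0.0367 → 0.0363 at a 10% share (−1.1%) and 0.0366 → 0.0357 at a 20% share (−2.5%). Five noise covariates: 0.03671 → 0.03677 (+0.2%). Mean z rose from 2.69 to 2.72 and from 2.77 to 2.82.

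**6. What this does to the halved arms.** Scaling the SEs in step 4 by √2 for 625 v 625, power = Φ(5/SE − 1.96). One-quarter baseline, 30% share: 1.394 → 1.322, power 94.8% → 96.6%. Four-quarter baseline, 30% share: 1.312 → 1.271, power 96.8% → 97.6%.

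**The case against.** The strongest reply is that the power sentence is only an add-on. Expected balance comes first, and the same model stands without the second reason. That is right: a sparse, pre-specified primary model is no error. But balance is an argument about bias. It does not make the statement about power true.

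Secondly, the model already holds baseline adherence, itself a practice-level measure and probably the strongest predictor. This stands, and it is why the remaining gain is small. It weakens where baseline rests on few patients. Replicate 3 expects 30,000 patients, or 6 per practice, and 1.5 per quarter if that is a yearly figure (an assumption). The reliability m × ICC/(1 + (m − 1) × ICC) is then 0.38 or 0.13, if the pilot ICC carries over.

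Thirdly, the larger gains need a one-quarter baseline, whereas Outcome measurement describes four quarters. This also stands; the four-quarter column is the better guide unless baseline adherence is taken from a single period.

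A reader might infer that the Analyses and Subgroup analyses sections contradict each other. They do not: a factor can be associated with the outcome, balanced by randomisation and left out of the model. The second section only makes it plausible that the omitted factors are prognostic. Nor does it follow that adjustment can never cost anything. With pure noise the SE rises by 0.1-0.2%, so the accurate claim is that it never costs anything material.

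**Conclusion.** The concern holds in limited form. The statement that more practice characteristics would reduce power is wrong at this trial's size. Five useless terms cost at most about 0.2 point of power in any two-arm contrast, and prognostic terms raise power slightly.

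The precision forgone is small: about 1-3% of the SE with a four-quarter baseline and up to about 5% in replicate 3 with a one-quarter baseline. These figures rest on an assumed 10-30% of between-practice variance explained, the pilot ICC carried over to other outcomes, and the assumed spread of practice sizes.

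It would be tempting to conclude that the primary analysis is biased or underpowered. The documents do not support that. The sparse model gives a valid comparison, power for 5 points is already about 95% or more in the smallest contrast examined, and no conclusion is likely to turn on the choice.

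**What to change.** Delete the power sentence. Pre-specify in the primary model, besides arm and baseline adherence, the five characteristics already planned for subgroups: solo or group practice, urban or rural location, practice volume, physician sex and years since graduation. The last two need aggregating to practice where physicians share an address. Report the model with arm and baseline adherence alone as a sensitivity analysis.

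The cost is a wording change and a few model terms from variables the subgroup analyses need anyway. The odds ratio becomes conditional on more covariates, so report the absolute difference alongside it.

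If the sparse model is kept as primary, justify it by simplicity and expected balance, not by power.
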